### Measurements

The measurements used in the protocol will be taken before and after the intervention period (16 weeks). The study protocol flow of participants is outlined in Fig. 1. The post-intervention test will be scheduled the following week after finishing the 16-week intervention period. The primary outcome variable is cardiorespiratory fitness, measured through VO_2peak_. The secondary outcome variables include left ventricular function, body composition, biochemical profile, vascular endothelial function, dietary adherence, the state of depression and anxiety, and health-related quality of life. The SPIRIT figure showing the respective time points for assessments and intervention is provided in Fig. 2.

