#### Anthropometry and body composition

Anthropometry includes stature (SECA 213), total body mass (SECA 869), BMI calculated as (total body mass [kg]/stature [m^2^]), and waist and hip circumferences (SECA 200) to calculate waist:hip ratio. All measurements will be taken in accordance with guidelines from the International Society for the Advancement of Kinanthropometry [24]. Furthermore, fat-free mass, total body water, and fat mass will be estimated with bioelectrical impedance analysis (Tanita, BF 350 and Tanita, BC-418 MA).

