### Data analysis

The primary outcome variable of this study is VO_2peak_. A priori power analysis (G*Power 3 statistical software) [48] was performed to calculate the average sample size. Due to the lack of any source on the effect of VO_2peak_ in MI patients, we speculate a similar increase based on a study of coronary artery disease [49]. Therefore, we assume a mean change of 5.0 mL kg^−1^ min^−1^ and a common standard deviation (SD) of 4.0 for participants allocated to the HIIT groups and a mean change of 3.0 ± 4.0 mL kg^−1^ min^−1^ for participants allocated to the AC group. Based on 1:1:1 randomization to three treatment arms with equal group size, we expect that pre-post intervention differences in our design would be achieved with 177 people (59 each group, α = 0.05, Cohen medium effect size f = 0.23, 80% power). Assuming a maximum loss of follow-up of 10%, the plan will be to recruit a total of 194 individuals. The statistical analysis will be performed using IBM SPSS Statistics, Version 22.0 (IBM Corp., Armonk, NY, USA). In the final analysis, four comparisons will be made: HIIT groups vs AC; HV-HIIT vs LV-HIIT; HV-HIIT vs AC; and LV-HITT vs AC. Two parametric tests will be performed after all assumptions for each test are met. For comparisons between groups at baseline, one-way analysis of variance (ANOVA) or the non-parametric method of Kruskal–Wallis and Chi-square test will be used. A linear regression model with ANOVA will be used to assess training effects on the primary and secondary study outcomes. We will examine the delta (Δ) score for each group (AC, HV-HIIT, LV-HIIT), adjusting for age, sex, changes in body mass, and the initial value of each of the dependent variables. Helmert contrasts will be performed to analyze the difference between the two exercise groups pooled together and the AC group. Bonferroni correction was used to determine the level of significance when a significant main effect was found. The differences between dropouts and participants who remain in the study will be examined; the data will be analyzed according to the intention-to-treat principle [50]. For each outcome variable, the effect size and the level of significance corresponding to the main group (between-subjects), time (within-subjects), and interaction (group × time) will be reported. To prevent type I error, post hoc comparisons (pre vs post by group) will be performed when a significant interaction effect is present. Values will be expressed as mean ± SD. The significance level will be set at 5% (α = 0.05). Practical significance will be assessed by calculating Cohen’s *d* effect size. Effect sizes (*d*) > 0.8, in the range of 0.5–0.8, in the range of 0.2–0.5, and < 0.2 will be considered as large, moderate, small, and trivial, respectively.

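### The outcome model adjusts for change in body mass, a post-randomisation variable, so it does not estimate the intention-to-treat effect; the size and direction of the bias cannot be known in advance

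*Protocol article*

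**What the plan says.** The primary outcome is defined in the Measurements section: "The primary outcome variable is cardiorespiratory fitness, measured through VO_2peak". That definition carries no unit. The unit appears in Data analysis, where the sample size is derived: "we assume a mean change of 5.0 mL kg^−1^ min^−1^ and a common standard deviation (SD) of 4.0" in the HIIT groups, and "a mean change of 3.0 ± 4.0 mL kg^−1^ min^−1^ for participants allocated to the AC group". The result is "177 people (59 each group, α = 0.05, Cohen medium effect size f = 0.23, 80% power".

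For the outcome analysis, Data analysis specifies a linear regression on the change score, "adjusting for age, sex, changes in body mass, and the initial value of each of the dependent variables". It applies this to the primary and the secondary outcomes and excepts none. The same section commits to intention to treat, and separately promises group, time and group × time effects for each outcome variable, with no body-mass covariate stated for that report.

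Body mass is measured before and after the 16 weeks. Measurements states: "The secondary outcome variables include left ventricular function, body composition, biochemical profile". The section on anthropometry and body composition begins: "Anthropometry includes stature (SECA 213), total body mass (SECA 869), BMI". Bioimpedance measures of fat mass, fat-free mass and body water follow in the same section.

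**The concern.** Age, sex and the baseline value of the outcome are fixed before allocation, so adjusting for them leaves the randomised comparison intact. Change in body mass is different. It is observed at the end of the intervention, and supervised exercise, activity advice and repeated dietary counselling can all alter it. Conditioning on it sets aside whatever part of the programme effect runs through weight. It can also introduce confounding by anything that drives both weight change and fitness, such as adherence. The coefficient that results is neither the effect of assignment nor a defined direct effect, and the article states no mediation or direct-effect aim.

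For the primary outcome the link is also mechanical: on a per-kg scale, weight change enters the outcome through its denominator. The comparison of the two HIIT volumes uses the same model and is exposed in the same way if they differ in weight change.

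**Working it through.** **1. The plan's own figure.** Inputs from Data analysis: mean changes 5.0, 5.0 and 3.0, SD 4.0, three equal arms ("Based on 1:1:1 randomization to three treatment arms with equal group size").

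- Grand mean = (5 + 5 + 3)/3 = 4.33.
- SD of the means = √[(0.667² + 0.667² + 1.333²)/3] = 0.943.
- f = 0.943/4 = 0.2357.
- One-way ANOVA with non-centrality N·f² needs N = 177 for 80% power (power 0.801).

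The 177 is reproduced; the printed 0.23 is 0.2357 truncated. The design is thus powered on a total difference of 5.0 − 3.0 = 2.0 mL/kg/min, with nothing taken out for weight.

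**2. Weight change through the denominator.** If absolute oxygen uptake is unchanged, an arm at v mL/kg/min and w kg that loses d kg more than its comparator gains v·w/(w − d) − v. The article gives neither w nor v, so both are assumed: 75–85 kg and 20–25 mL/kg/min.

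- Smallest shift for 1 kg: 20 × 85/84 − 20 = 0.24, which is 12% of 2.0.
- Largest shift for 1 kg: 25 × 75/74 − 25 = 0.34, which is 17% of 2.0.
- For 2 kg the range is 0.48–0.68, or 24–34% of 2.0.

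The shift favours whichever arm loses more weight.

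**3. What the adjusted model returns.** The adjustment takes out the fitted slope on mass change times the between-arm difference in mass change. That equals the shift in step 2 only if the slope is the denominator slope. An illustrative simulation makes that assumption: 600 runs, 59 per arm, 80 kg, 22 mL/kg/min, SD of mass change 2.5 kg, total effect fixed at 2.0, HIIT pooled against control, baseline VO2peak in the model.

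| Extra weight loss in HIIT (kg) | Mean estimate with mass change | Power with mass change |
|---|---|---|
| −2 (control loses more) | 2.57 | 0.97 |
| −1 | 2.23 | 0.94 |
| 0 | 1.98 | 0.87 |
| 1 | 1.72 | 0.77 |
| 2 | 1.37 | 0.52 |
| 3 | 1.11 | 0.34 |

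Without the covariate the mean estimate stayed between 1.94 and 2.03 in every row, and power between 0.86 and 0.88. The higher power in the first two rows comes from an inflated estimate and is no gain.

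**4. Body mass and BMI as outcomes.** With change in body mass, ΔW, as the outcome, the model reads ΔW = a + b·group + c·ΔW + other terms. Least squares fits this perfectly with c = 1 and b = 0. In the simulation b was zero to machine precision (below 1e-13) whatever the true difference. BMI change is ΔW/height². With an assumed height of 1.70 m (SD 0.08), the model R² was 0.98–0.99 and the mean group coefficient was within 0.002 of zero, although true differences ran up to about 1 kg/m². Fat mass, fat-free mass and waist:hip ratio are not determined by ΔW, so a test can be run, but not of the total effect.

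**The case against.** A physiologist might defend the covariate as a way to separate a gain in oxygen uptake from a fall in weight. The question is legitimate, but the article does not pose it. It speaks of training effects under intention to treat, and absolute VO2peak in mL/min addresses the question without conditioning on a post-randomisation variable.

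A reader might infer that the adjustment necessarily removes part of the HIIT benefit. The article does not support that. Dietary recommendations go to all arms, and the two-weekly weighing and counselling is described for participants without restriction. Controls are advised to do at least 30 minutes of moderate exercise on 5–7 days a week, against two supervised sessions in the HIIT arms. Controls could lose as much weight or more.

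A reader might also infer that the plan makes the body-mass outcomes untestable. That is too strong. The secondary outcome named is body composition; that total body mass and BMI are tested under it is plausible but inferred. The promised group × time report may still test them. The full analysis plan, not shown here, may exempt an outcome from being its own covariate.

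Finally, the per-kg unit comes from the power calculation and not from the outcome definition. If the analysed outcome were in mL/min, the denominator argument would fall away. The post-randomisation argument would not.

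**Conclusion.** The covariate error stands. As written, the main model conditions on a variable that the programmes can change. It therefore estimates neither the effect of assignment that the plan claims nor the 2.0 mL/kg/min difference for which it is powered.

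The consequence is bounded only by assumption. On the assumed ranges for weight and fitness, the denominator alone contributes 12–17% of the planned difference per kg of between-arm difference in weight change. The bias is towards zero if HIIT loses more, away from zero if control loses more, and nil by this route if losses are equal. The simulated estimates (2.57 down to 1.11 for a true 2.0) illustrate sensitivity and do not predict the result.

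The body-mass and BMI result is algebraic (exact for the first, near-exact for the second). It applies only if those variables are analysed with this model read literally. The sample size itself is not in dispute.

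**What to change.** Delete change in body mass from the main model for the primary and all secondary outcomes. Keep age, sex and the baseline value of the outcome. If body size is wanted in the model, baseline BMI is already a stratification factor and is a valid baseline covariate.

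If the role of weight change is of interest, report absolute VO2peak (mL/min) as a labelled supportive analysis, or a mass-adjusted model as a labelled exploratory one.

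The cost is one phrase, settled before the outcome data are analysed. It needs no new measurements or participants, and the 177 stands because it was calculated for the total difference.

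### The stated 80% power belongs to the omnibus F test; the comparisons that answer the hypotheses have other powers, which depend on a Bonferroni rule of unstated scope

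*Protocol article*

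**What the plan says.** All of the relevant text is in the protocol article, section Data analysis.

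- **Endpoint and assumptions.** "The primary outcome variable of this study is VO_2peak". For the two exercise arms, "we assume a mean change of 5.0" mL/kg/min with "a common standard deviation (SD) of 4.0 for participants allocated to the HIIT groups"; for AC, "a mean change of 3.0 ± 4.0".
- **Sample size.** "Based on 1:1:1 randomization to three treatment arms with equal group size", the plan arrives at 177 people, 59 per arm, with α = 0.05 and "Cohen medium effect size f = 0.23, 80% power".
- **Comparisons.** Four are listed: pooled HIIT vs AC, HV-HIIT vs LV-HIIT, HV-HIIT vs AC, and LV-HIIT vs AC. For the first, "Helmert contrasts will be performed to analyze the difference between the two exercise groups pooled together and the AC group".
- **Multiplicity.** "Bonferroni correction was used to determine the level of significance when a significant main effect was found". The text does not give the divisor, does not say which comparisons are corrected, and does not say whether the Helmert contrast is among them.
- **Power per comparison.** None is given.
- **Adjustment.** Change scores are adjusted for age, sex, change in body mass and the baseline value.

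**The concern.** The first hypothesis (Background) is that supervised HIIT improves cardiovascular health more than physical activity recommendations alone. The pooled HIIT vs AC contrast and the two arm-specific contrasts address it. A significant three-group F test shows only that the three means are not all equal. If 177 was sized on that F test, the 80% does not describe the tests from which conclusions will be drawn. A Bonferroni step placed after the F test would lower their power further, perhaps without need. What is at stake is a missed effect on the primary outcome, and readers who believe the key contrasts have 80% power.

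**Working it through.** **Inputs** (Data analysis): mean changes 5.0, 5.0 and 3.0; SD 4.0; 59 per arm; α = 0.05. Sidedness is not stated, so contrasts are taken as two-sided. All powers are unadjusted for covariates and use the 177 evaluable participants.

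**1. Reproduce the stated figure.** The grand mean is 13/3 = 4.333, so the deviations are 0.667, 0.667 and −1.333.

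f = √[(0.667² + 0.667² + 1.333²)/3] / 4 = 0.943/4 = 0.2357

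λ = f² × N = 0.05556 × 177 = 9.83

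Noncentral F with 2 and 174 df gives a power of 80.1%, and 177 is the smallest balanced total that reaches 80%. The printed f = 0.23 is this value shortened; taken literally, it would give 78.0%. The plan's 80% is therefore omnibus power.

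**2. Noncentrality of the planned contrasts.**

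- Pooled HIIT vs AC: 2 / [4 × √(1/118 + 1/59)] = 2/0.638 = 3.136
- One arm vs AC: 2 / [4 × √(2/59)] = 2/0.736 = 2.716

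Ungated powers come from the noncentral t with 174 df. Gated powers come from 1,000,000 simulated trials or more.

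| Reading of the plan | Pooled HIIT vs AC | Each arm vs AC | Both arms vs AC |
|---|---|---|---|
| Omnibus gate, α/4 for all four | 72.9% | 57.7% | 41.5% |
| Omnibus gate, α/3 | 75.9% | 61.6% | 46.1% |
| Omnibus gate, no Bonferroni | 79.4% | 72.1% | 64.1% |
| No gate, no Bonferroni | 87.7% | 77.1% | – |
| Helmert gate at 5%, no Bonferroni | 87.7% | 75.5% | 64.8% |

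At α/4 the omnibus gate removes nothing further; at α/3 it removes less than half a percentage point. If Bonferroni covers only the three pairwise comparisons, each arm has the α/3 figure and the pooled contrast keeps 79.4% (gated) or 87.7% (ungated).

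**3. What Bonferroni accounts for.** Under the omnibus gate, dividing by four lowers each arm from 72% to 58% and the pooled contrast from 79% to 73%. The gap from 80% down to 72% (gated) or 77% (ungated) for each arm is there before any correction, because the trial was sized on the omnibus test.

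**4. Is Bonferroni needed?** The four nulls are HV = AC, LV = AC, HV = LV, and (HV + LV)/2 = AC. Any two of them together force all three means to be equal. So once the means are not all equal, at most one null is true, and a valid 5% gate is enough. Simulated family-wise error with all comparisons at 5% (2,000,000 trials per configuration; nonzero differences of 3):

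| True nulls | Omnibus gate | Helmert gate |
|---|---|---|
| All four | 5.0% | 5.0% |
| Only HV = AC | 5.0% | 2.5% |
| Only HV = LV | 5.0% | 5.0% |
| Only the pooled null | 5.0% | 5.0% |

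With no gate, four tests at 5% each give a family-wise error of 12.8% when all means are equal.

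**The case against.** **The divisor and its scope are not in the text.** This stands. The Helmert contrast has its own sentence, before the Bonferroni one, and no correction is attached to it. A reader might infer that the main hypothesis is tested at 73% power. That is the least favourable of several readings; if the Helmert contrast is uncorrected it has 79% to 88%, and no material shortfall follows.

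**The gate is itself a reading.** This also stands. The four comparisons are announced without condition, and the reference to a main effect strictly qualifies the correction. Explicit gating appears only for pre-post comparisons within groups, after a significant interaction. A reader might infer that Bonferroni is plainly redundant. That holds only if the comparisons wait for a significant main effect, which is the natural reading but not the only one.

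**Bonferroni is not the sole cause.** This stands too. A reader might attribute the whole shortfall to it, but sizing on the omnibus test explains part of the per-arm gap.

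**The planned analysis adjusts for covariates.** This is fair. The document gives no correlation, so the gain can only be illustrated by assumption. At α/4, covariates explaining 15% of the variance would bring the pooled contrast to 80.9%, and 35% would bring each arm to 80.0%.

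**A conservative correction is no error, and details may sit in an analysis plan.** This stands only in part. The article itself states a power, a correction and a condition for it; as they stand, the power does not apply to the listed comparisons.

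**Conclusion.** The concern holds in limited form. The 80% is power for the 2-df omnibus test. Without covariate gain, each arm vs AC is below 80% on every reading: about 58% to 62% with Bonferroni, and at most 77% without it. Pooled HIIT vs AC lies between about 73% and 88%, and the text does not settle where. If the comparisons are gated by a significant main effect, Bonferroni costs power without buying needed error control; if they are not gated, some control is needed.

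These figures rest on the plan's own means and SD, 59 evaluable per arm, two-sided tests and no covariate gain. The documents do not support a single shortfall stated as fact, nor a claim that type I error is at risk under the gated reading. The point is worth acting on because the protocol reports that recruitment is finishing (Trial status), so the analysis rule is the practical lever. Reaching 80% at α/4 would take 68 per arm (204 in total) for the pooled contrast and 91 per arm (273) for each arm vs AC.

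**What to change.** Before outcome data are examined:

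1. Name the Helmert contrast, pooled HIIT vs AC, as the primary test at two-sided 5%, with no omnibus gate before it.
2. Only if it is significant, test HV-HIIT vs AC, LV-HIIT vs AC and HV-HIIT vs LV-HIIT, each at 5% without Bonferroni. The HV vs LV comparison must sit behind the gate as well.
3. State that the 80% is omnibus power. Restate unadjusted power as about 88% for the pooled contrast and about 75% for each arm vs AC.

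An alternative closer to the present text is to make the omnibus gate explicit for all four comparisons and drop Bonferroni, which gives about 79% pooled and 72% per arm.

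**Cost.** No extra participants or measurements are needed, and the contrast is already in the plan. It is nevertheless a change to the primary analysis late in the trial, so it should be dated and documented as made without sight of outcomes. The Helmert gate is less sensitive than the omnibus test if the two HIIT arms differ from AC in opposite directions, and HV vs LV is not formally tested if the gate fails.

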
On the other hand, the relevance of overall high-quality food patterns, rather than focus on single nutrients and foods, has emerged as a powerful paradigm to address the diet and to assess their potential cardiovascular disease preventative effects [21]. The Mediterranean diet (Mediet), representing the dietary pattern usually consumed among the populations bordering the Mediterranean Sea, has been widely reported to be a model of healthy eating for its contribution to a favorable health status and a better quality of life, reducing overall mortality from cardiovascular diseases [22].

Considering all the above-mentioned points, the INTERFARCT study is designed to investigate what effect different 16-week supervised aerobic INTERval exercise programs (HV vs LV) with Mediet recommendations will have in people after suffering an acute myocardial inFARCTion compared to AC that is recommended a Mediet and physical activity without supervision sessions.

We hypothesize that: (1) supervised HIIT will get superior improvements in cardiovascular health than only physical activity recommendations; and (2) a high-intensity and LV exercise program will get similar results compared to a high-intensity and HV exercise program. Therefore, the primary objective of this randomized controlled trial (RCT) will be to assess the effects of different programs of HIIT and Mediet recommendations on overall health, cardiorespiratory fitness, biomarkers, ventricular function, and perception of quality of life after MI compared to only physical activity recommendations. The secondary objectives will be: (1) to analyze the differences in the studied variables between the two HIIT programs (HV vs LV) with Mediet recommendations to observe the effect of exercise volume; and (2) to analyze whether a treatment with only recommendations (exercise and diet) is effective in the secondary prevention of cardiovascular disease compared to supervised exercise.

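### A significant group × time interaction is followed by within-arm pre-post tests, which cannot show which arms differ; the between-arm comparisons already listed should follow instead

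*Protocol article*

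**What the plan says.** Everything below is in the protocol article, under Data analysis, unless another section is named.

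- The training effect has an assigned model: "A linear regression model with ANOVA will be used to assess training effects on the primary and secondary study outcomes". It is fitted to the change score by arm, with age, sex, change in body mass and the baseline value of the outcome as covariates.
- Four between-arm comparisons are listed: pooled HIIT against AC, high volume against low volume, and each HIIT arm against AC. A Helmert contrast of pooled HIIT against AC is also specified.
- For every outcome, effect sizes and significance levels will also be reported for "main group (between-subjects), time (within-subjects), and interaction" of group with time. The text does not say whether this second model carries the covariates of the first.
- The follow-up to that interaction is stated: "post hoc comparisons (pre vs post by group) will be performed when a significant interaction effect is present". The reason given is protection against type I error.
- Bonferroni correction has a different trigger, a significant main effect.

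**The concern.** A significant interaction says that the arms changed by different amounts. The next question is which arms differ and by how much. A pre-post test within one arm asks something else: whether that arm's mean change is zero. Its answer mixes any treatment effect with whatever else moves between two visits, such as regression to the mean or familiarity with the exercise test. Randomisation does not protect it.

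The stated reason does not hold either. Running within-arm tests only after a significant interaction does not limit the error rate for HIIT against AC or for high against low volume, because none of those differences is being tested.

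What is at stake is interpretation. If every arm shows a significant improvement, a report can slide into saying that recommendations alone worked, or that the two volumes are similar because both improved. Neither statement follows from the within-arm tests.

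**Working it through.** **Inputs, all from Data analysis.** HIIT arms: "we assume a mean change of 5.0 mL" per kg per min, with "a common standard deviation (SD) of 4.0 for participants allocated to the HIIT groups". AC: "a mean change of 3.0 ± 4.0 mL" in the same units. Design: "59 each group, α = 0.05, Cohen medium effect size f = 0.23, 80% power".

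**1. The plan's own figure.** The arm means 5, 5 and 3 have grand mean 13/3 = 4.333. Their standard deviation is √[(0.667² + 0.667² + 1.333²)/3] = 0.943, so f = 0.943/4.0 = 0.2357. A one-way three-group F test at α = 0.05 with N = 177 then has 80.1% power. The stated 177 is reproduced, and the printed f of 0.23 is 0.2357 cut to two decimals. The planned test is therefore a between-arm test on the change score.

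**2. The within-arm tests.** Expected paired t = mean change / (SD/√n), with SD/√n = 4.0/√59 = 0.521.

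| Arm | Expected t | Power, two-sided 0.05 |
|---|---|---|
| AC | 3.0/0.521 = 5.76 | 99.99% |
| Each HIIT arm | 5.0/0.521 = 9.60 | above 99.99% |

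At α = 0.05/3 the AC test still has 99.94% power. In 20,000 simulated trials under these assumptions, the unadjusted interaction was significant in 80.2%. In all of those trials all three within-arm tests were significant (99.9% with Bonferroni at 0.05/3).

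**3. The between-arm comparisons under the same assumptions** (difference 2.0, SD 4.0).

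- Pooled HIIT against AC: 2/(4√(1/118 + 1/59)) = 3.14, power 87.7% at 0.05.
- One HIIT arm against AC: 2/(4√(2/59)) = 2.72, power 77.1% at 0.05, 61.8% at 0.05/3 and 57.7% at 0.05/4.
- High against low volume: the assumed difference is 5.0 − 5.0 = 0, yet both within-arm tests are near certain to be significant.

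The within-arm results would thus look the same whether or not a given pair of arms differs.

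**4. How far this depends on the assumptions.** With SD 4.0, power of the AC within-arm test is 96.5% if the true AC change is 2.0, 80.9% if 1.5 and 47.1% if 1.0. With a change of 3.0 and SD 8 it is 80.9%. The article gives no planning figures for secondary outcomes, so nothing comparable can be computed for them.

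**5. The second model, if it omits the covariates.** With two visits, an unadjusted group × time interaction is the one-way ANOVA of the change score, a second test of the same effect. Assume that baseline correlates with change at 0.2 to 0.4 in absolute value (not in the article). The residual SD, 4√(1 − r²), is then 3.92 to 3.67, and adjusted power is 82% to 87% against 80% unadjusted. In simulation the two tests fall on opposite sides of 0.05 in about 5% to 10% of trials. Taking whichever is significant gives a type I error of about 6% to 7%. If the second model keeps the covariates, including baseline, its interaction test coincides with the adjusted change-score test and this step falls away.

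**The case against.** The strongest reply is that the plan already holds the right comparisons. The same section lists every pairwise comparison and the pooled contrast, and it gives the adjusted change-score model the job of assessing training effects. The within-arm tests are then additional output. This stands. A reader might infer that HIIT is never properly tested against AC, or that two rival primary analyses of equal standing are planned, and the text supports neither.

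A reader might also take secondary objective 2 (Background) as a plan to judge recommendations alone from within-arm change, since it sets out "to analyze whether a treatment with only recommendations (exercise and diet) is effective in the secondary prevention of cardiovascular disease". The sentence goes on to make supervised exercise the comparator, so the objective is itself a between-arm question.

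Two further limits stand. It is tempting to say that the within-arm tests will be significant in every arm for every outcome, but that is shown only for VO2peak under the planning assumptions. And the interaction is a second, less precise test only if the covariates are dropped, which the article does not say. Naming a confirmatory model more explicitly could also be left to an analysis plan that is not shown.

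The reply does not reach the follow-up rule itself. That rule is stated, not omitted. It attaches the wrong tests to a significant interaction and gives a reason that does not apply to them.

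**Conclusion.** The point holds in a limited form. The stated follow-up to a significant interaction tests each arm against zero change. It is not a randomised comparison and does not control error for the comparisons of interest. For VO2peak, with changes of 3.0 and 5.0, SD 4.0 and 59 per arm, it is near certain to be significant in all three arms (expected t 5.76 and 9.60) and so cannot show which arms differ. With a true AC change of 1.0 the AC test has 47.1% power, so significance in every arm is then not assured; the test would still not compare arms. Valid between-arm comparisons are in the plan, but the interaction is not followed by them. The possible duplicate test is a conditional and smaller matter.

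**What to change.** - Name the adjusted change-score model as the confirmatory analysis, with pre-randomisation covariates only: baseline value, age and sex. Leave out change in body mass, which arises after randomisation and may itself be affected by the intervention.
- Follow it with the four between-arm comparisons already listed, each with a 95% confidence interval, under one stated multiplicity rule.
- Replace the pre-post tests by group with within-arm mean changes and SDs, shown descriptively without p-values.
- Treat any group, time and interaction output as supportive only, and state whether that model carries the covariates.

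The cost is analysis wording and fewer tests. No further participants or measurements are needed. The article reports recruitment as nearly complete at submission, so the change should be documented before outcome data are analysed.
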